#### Endoscopic mucosal resection

Endoscopic mucosal resection is performed as described by Karita and Hurlstone[9,15]. At the discretion of the endoscopist, conscious sedation is used with 2.5–10 mg midazolam and/or 25–100 μg of fentanyl. An endoscope (gastroscope or sigmoidoscope) is inserted into the rectum and air insufflation via the endoscope will provide proper distension of the rectum. The submucosa underneath the lesion will be injected through an endoscopic injection catheter with a solution of saline 0.9%, 1 ml methylene blue, and 1:10,000 units adrenaline in order to lift the adenoma (no upper volume limit). A (barbed or standard) resection snare will be placed around a part of the lesion and subsequently tightened for resection through the submucosal layer by electro-coagulation. Each part of the adenoma will be resected by this piecemeal fashion until the entire lesion is macroscopically removed and the blue colored submucosa is visualized. Visible submucosal vessels will be treated by endoscopic clips or electro-coagulation to prevent delayed bleeding. Hereafter, the edges of the mucosal defect and potential remnants within the resection crater will always be treated with APC to increase adenoma clearance. If bleeding during the procedure precludes 100% clearance of the adenoma, the EMR procedure will be continued after 1 day until all adenomatous tissue is resected. In case of procedural blood loss of > 100 mL or if delayed perforation is anticipated on procedural grounds, patients are admitted to the hospital for observation; otherwise, they are discharged after the procedure in accordance with current practice.

After 3 months the treating endoscopist will perform a control endoscopy. If presumed residual disease is seen, biopsies will be taken to confirm the presence of neoplasia by histology. Hereafter, the residual adenomatous tissue will be resected endoscopically by either EMR (if > 5 mm) or APC (if < 5 mm). Any intervention by EMR/APC at 3 months is part of the EMR treatment strategy.

### Informed consent procedure

Consecutive eligible patients will be recruited at the outpatient clinic in the participating centers by the involved physician (surgeon or gastroenterologist). Patients fulfilling the abovementioned inclusion criteria will be informed about the study by the physician. After written informed consent, patients will be allocated to either TEM or EMR by computerized block randomization with variable block size via the study website . The patient will subsequently be scheduled for therapy in the participating centre. Patients unable or refusing to provide informed consent will be treated according to current clinical practice.

### Intervention failure

When for technical reasons EMR procedures turn out not to be performable after randomization, the patient will automatically undergo the TEM treatment strategy. When TEM turns out not to be performable, an attempt with EMR will be done as well. When adenomas turn out to be too large or too high in the rectum for TEM by the Storz equipment, the patient will undergo TEM in another hospital where Wolf equipment is available.

### Safety monitoring

In order to control for quality of the treatment (TEM or EMR) all procedures will be taped for reference. The first 3 procedures and an additional random sample per specialist will be assessed for quality by an expert panel at 2 time points during each year.

### Histopathological evaluation

Resection specimens after TEM will be stretched and pinned on a cork plate before immersion into formalin. After standard processing the resection specimen will be transected each cm for evaluation by a gastrointestinal pathologist. The lateral and basal resection margins will be evaluated for absence of neoplasia, when possible. All resected pieces by EMR will be processed in the same manner, and only the basal resection margins will be evaluated.

The risk of lymph node metastases is increased in case of neoplasia extending into the submucosal layer, poor tumor differentiation, mucinous cancer, vascular invasion and tumor budding, all of which warrant further radical surgery [57-60]. By strict adherence to the inclusion criteria, the risk of invasive cancer is reduced to 1.6–3%[56,61]. In case of an unexpected invasive cancer despite adherence to the inclusion criteria, the patient will be excluded after the histopathological evaluation (late exclusion). In case of intramucosal cancer (i.e. not invading through the muscularis mucosae), both TEM and EMR will be regarded as sufficient treatment when the lesion is radically removed.

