**Methods/design:**

Multicenter randomized trial among 15 hospitals in the Netherlands. Patients with a rectal adenoma ≥ 3 cm, located between 1–15 cm ab ano, will be randomized to a TEM- or EMR-treatment strategy. For TEM, patients will be treated under general anesthesia, adenomas will be dissected en-bloc by a full-thickness excision, and patients will be admitted to the hospital. For EMR, no or conscious sedation is used, lesions will be resected through the submucosal plane in a piecemeal fashion, and patients will be discharged from the hospital. Residual adenoma that is visible during the first surveillance endoscopy at 3 months will be removed endoscopically in both treatment strategies and is considered as part of the primary treatment.

Primary outcome measure is the proportion of patients with recurrence after 3 months. Secondary outcome measures are: 2) number of days not spent in hospital from initial treatment until 2 years afterwards; 3) major and minor morbidity; 4) disease specific and general quality of life; 5) anorectal function; 6) health care utilization and costs. A cost-effectiveness and cost-utility analysis of EMR against TEM for large rectal adenomas will be performed from a societal perspective with respectively the costs per recurrence free patient and the cost per quality adjusted life year as outcome measures.

Based on comparable recurrence rates for TEM and EMR of 3.3% and considering an upper-limit of 10% for EMR to be non-inferior (beta-error 0.2 and one-sided alpha-error 0.05), 89 patients are needed per group.

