### Sample size calculation

Assuming a baseline recurrence rate of 3.3% for both TEM and EMR (average recurrence based on a systematic review) and considering an upper limit of 10% for EMR to be non-inferior, with a β-error of 0.2 and α-error of 0.05, 89 patients are needed per randomization group. As unexpected invasive cancers are expected in maximally 3% of patients, the total sample size will be 184 patients.

Since EMR is known to be effective in even more than 2 attempts, an upper limit of 10% seems reasonable, whereas higher recurrence rates would lead to many additional procedures which renders this strategy impracticable and probably not cost-effective.

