### Data-analysis

Since the main outcome of this study is the neoplasia recurrence rate, i.e. proportion of patients with recurrent disease, the Chi-square test will be used to compare the intervention groups (TEM versus EMR). Since the event of recurrence, and not time to recurrence, is the most important indicator for treatment failure, Kaplan Meier methods will not be used. The complication and mortality rates will be compared in the same manner. The number of days not spent in hospital as additional primary outcome measure will be compared by the Wilcoxon rank sum test.

Differences between the intervention groups in continuous outcome measures (e.g. Wexner incontinence scale, quality of life questionnaires) will be tested by the student's t-test or Wilcoxon rank sum test, where appropriate.

All analyses will be carried out primarily on an intention-to-treat basis.

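### Late exclusion of randomised patients with unexpected invasive cancer contradicts the stated intention-to-treat analysis and, on its natural reading, also removes them from the cost and safety comparisons

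*Protocol article*

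**What the plan says.** Allocation precedes treatment (Informed consent procedure): "After written informed consent, patients will be allocated to either TEM or EMR by computerized block randomization with variable block size".

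The Histopathological evaluation section then deals with lesions that turn out to be invasive cancer although the inclusion criteria were met: "the patient will be excluded after the histopathological evaluation (late exclusion". It puts this risk at 1.6–3% and states that neoplasia extending into the submucosa is among the findings that call for further radical surgery.

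The Sample size calculation allows for the loss: "As unexpected invasive cancers are expected in maximally 3% of patients, the total sample size will be 184 patients".

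The Data-analysis section states: "All analyses will be carried out primarily on an intention-to-treat basis". It names no modified set and no exception for late exclusions.

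The specimen that decides the exclusion differs by arm. The abstract says of TEM that "adenomas will be dissected en-bloc by a full-thickness excision" and of EMR that "lesions will be resected through the submucosal plane in a piecemeal fashion". For the TEM specimen, "The lateral and basal resection margins will be evaluated for absence of neoplasia, when possible". For EMR, "All resected pieces by EMR will be processed in the same manner, and only the basal resection margins will be evaluated".

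**The concern.** An analysis that drops patients because of something found after randomisation is not an intention-to-treat analysis. The sample-size inflation shows that the drop is planned, so two parts of the article define different analysis populations.

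Two things are at stake.

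- **The non-inferiority comparison.** The finding that triggers exclusion is read from a specimen whose form depends on the arm. Blinding is stated for the surveillance endoscopists and for the panel judging readmissions. None is stated for the pathologist, and an en-bloc specimen is easily told from pieces. If invasion were recognised more often in one arm, the patients remaining would no longer be comparable. Few recurrences are expected, so a few exclusions could matter.
- **The economic and safety comparisons.** The main objective is cost-effectiveness and cost-utility, evaluated from a societal perspective. Exclusion without qualification most naturally means exclusion from everything: complications, mortality, days outside hospital, quality of life, costs and QALYs. Yet these patients face further radical surgery, and its consequences belong to whichever strategy they were allocated to. The article plans a sensitivity analysis for unrelated readmissions that fall unevenly between arms. It plans none for these exclusions, which do relate to the target lesion.

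**Working it through.** **Inputs from the article.** Recurrence 3.3% in both arms; upper limit 10% for EMR, hence a margin of 10 − 3.3 = 6.7 points; one-sided alpha 0.05 (abstract); power 80%; 89 per arm; total 184, or 92 per arm; invasive cancer 1.6–3%.

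**1. The plan's own figures.** With unpooled variance,

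n = (1.645 + 0.842)² × 2 × 0.033 × 0.967 / 0.067² = 87.9, so 88 per arm. The article states 89, at which power is 80.4%.

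Inflation: 178 / 0.97 = 183.5, so 184. The arithmetic is sound. It also confirms that late exclusions are meant to be outside the analysed 178.

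**2. Size of the exclusion.**

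- Expected exclusions: 184 × 0.016 = 2.9 to 184 × 0.03 = 5.5.
- Expected recurrences: 178 × 0.033 = 5.9.

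Exclusions therefore number between about half and nearly all of the expected primary events. The two are different kinds of event; the comparison shows scale only.

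**3. Can the handling of these patients change the conclusion?** Assume 3 recurrences per arm and 6 cancers among 184. The one-sided 95% Wald upper limit for EMR minus TEM is d + 1.645 × √[p₁(1 − p₁)/n₁ + p₂(1 − p₂)/n₂].

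| Cancers, EMR / TEM | Handling | EMR | TEM | d (points) | Upper limit (points) |
|---|---|---|---|---|---|
| 3 / 3 | excluded | 3/89 | 3/89 | 0.0 | 4.5 |
| 3 / 3 | failures | 6/92 | 6/92 | 0.0 | 6.0 |
| 4 / 2 | excluded | 3/88 | 3/90 | 0.1 | 4.5 |
| 4 / 2 | failures | 7/92 | 5/92 | 2.2 | 8.2 |

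With an even split both analyses stay within 6.7 points. With 4 against 2 they disagree.

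Chance alone can produce such a gap. For two independent binomial counts with 92 per arm and equal true cancer rates, the probability that EMR has at least two more cancers than TEM is about 18% at a rate of 1.6% and 25% at 3%.

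**4. Cost of counting cancers as failures.** The failure rate per arm becomes c + (1 − c) × 0.033, and power at 92 per arm is Φ(0.067/SE − 1.645).

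- c = 0.016: rate 4.8%, SE = √(2 × 0.0485 × 0.9515/92) = 0.0317, power about 68%; 128 per arm needed for 80%.
- c = 0.03: rate 6.2%, SE = √(2 × 0.0620 × 0.9380/92) = 0.0356, power about 59%; 161 per arm needed for 80%.

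As the sole primary analysis this would change the endpoint and leave the trial underpowered. As a sensitivity analysis it is affordable.

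**The case against.** **Biased detection is not shown.** A reader might infer that invasion will be found less often in EMR pieces. The documents do not support that. Exclusion turns on depth of invasion, whereas the lateral margins read only after TEM concern completeness of resection. EMR pieces are processed like TEM specimens, and basal margins are read in both arms. Argon plasma is applied after the pieces have been taken, so it cannot alter them. This objection stands: unequal detection is a risk of unknown direction and size. In one plausible direction, a cancer missed after EMR stays in and may count as an EMR recurrence, which works against EMR.

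**A single recurrence does not clearly decide the verdict.** A reader might cite 4 EMR against 3 TEM recurrences at 89 per arm, which fails a score test. It fails by a hair (p = 0.0503), the article names no score test, and the Wald limit of 5.9 points passes. Sensitivity to single events comes from the low event count and would exist without the exclusion rule.

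**The exclusion can be defended for recurrence.** Invasion was present before randomisation, and such patients never had the condition under study. That stands, but it justifies a modified intention-to-treat set, named as such. The word primarily in the Data-analysis section does not define one.

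**Scope and cost are partly inferred.** The article does not list the analyses to which the exclusion applies, so removal from costs and quality of life is a reading, though the natural one. It gives no cost for the further surgery, so no euro figure is offered. If exclusions were balanced, much of the omitted cost would cancel in the incremental comparison.

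**Conclusion.** The contradiction is real and rests on the text alone. The histopathology rule and the sample-size inflation remove randomised patients; the analysis section says intention-to-treat without exception. The rule affects about 3 to 6 of 184 patients. On its natural reading it also takes patients facing further radical surgery out of a trial whose main objective is economic.

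The effect on the non-inferiority result is conditional. The shift from 4.5 to 8.2 points depends on the assumed 3 recurrences per arm, the assumed 4 to 2 split, a Wald limit and counting each cancer as a failure. It shows that the handling can matter, not that it will. No bias in either direction is established, and the sample-size calculation itself is not at fault.

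**What to change.** 1. Restrict the late exclusion to the recurrence endpoint and name that primary set modified intention-to-treat. The endpoint definition and the 89 per arm stay as they are.
2. Keep all randomised patients, with data collection continued, for days alive and outside hospital, complications, mortality, quality of life, costs and QALYs. State in advance how a finding of invasive cancer enters the count of days, since at present only recurrence and death end it.
3. Report the number of late exclusions by arm.
4. Pre-specify an all-randomised sensitivity analysis of recurrence in which invasive cancers count as failures of the allocated strategy, and state whether the non-inferiority conclusion changes.

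The cost is revised wording, follow-up of about 3 to 6 more patients, somewhat more variable cost estimates, and a sensitivity analysis with power of only about 59–68%. Because of that low power, failure to show non-inferiority there should be read together with the exclusion counts by arm. The change must be made before follow-up of excluded patients is dropped, because the missing data cannot be recovered at the analysis stage.

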### Outcome parameters

#### Primary outcome measure (for non-inferiority)

(1) Recurrence of neoplasia, defined as the presence of histologically proven neoplastic tissue in either visible recurrent lesions or in random biopsies, taken at surveillance endoscopies after the intervention strategy has been completed.

Any remnant adenoma identified and treated by EMR/APC at 3 months is considered part of the initial intervention strategy in both arms. Hereafter, patients will undergo surveillance endoscopies (with a GIF-Q160 endoscope) at 6, 12 and 24 months by an independent endoscopist who is blinded for the primary treatment. During each surveillance endoscopy recurrence will objectively be defined by the Higaki criteria for recurrence: tumor appearing within a clear resection scar; tumors with convergent folds; and tumors nearby a clear resection scar (within 5 mm)[49]. Targeted biopsies will be taken for histological confirmation; in case of an apparently healed normal scar without evidence of recurrence, 3 biopsies will be taken from the basis and 3 from the edges of the scar to detect occult recurrent neoplasia.

(2) Since equal recurrence rates for the TEM and EMR strategies are anticipated (equivalence trial), an additional outcome measure has been chosen that is responsive to both differences in initial care and to additional procedures that may be required in both strategies: the number of days that a patient is alive, outside the hospital and free of recurrence during two-year follow-up starting at the day of the initial treatment. Every patient therefore has potentially 730 days, and hospital days will be subtracted for initial treatment, readmissions, re-interventions and surveillance endoscopies. Adenoma recurrence or death will be considered as failure of the treatment strategy and no more additional days outside the hospital will be counted for such a patient.

'Unrelated' readmissions may have a relatively large impact on the number of days outside the hospital as well as on costs in this equivalence trial, if by chance they are unevenly distributed among treatment arms. Therefore, we will exclude the unrelated readmissions in a subsequent sensitivity analysis (both *clinically *and during the *cost-effectiveness and cost-utility analyses*), meaning that days in hospital due to clearly unrelated causes will not be subtracted from the total number of potential days outside the hospital for a patient. Likewise, other unrelated health care or unrelated days of sick leave will be excluded in this sensitivity analysis. Whether readmissions are related or unrelated to the target condition will be assessed by an independent expert panel (blinded for treatment).

The following standardized discharge criteria will be applied in all participating hospitals: normal intake of nutrition; normal mobility; absence of fever (< 38°C); and stable hemoglobin level during 1 day (< 1 mmol/L) in case of rectal blood loss.

#### Additional outcome measures

(a) Complications: subdivided into procedural (during treatment) and delayed complications (after ending the procedure); and further subdivided into major (requiring additional surgery) and minor (requiring endoscopic or medical intervention) complications.

During admission patients will be monitored for complications. In case of same day discharge from the hospital patients will be called by telephone 1 day after the procedure whether adverse events have happened. Two weeks after the intervention, a research nurse will contact the patient by telephone again and ask for occurred complications.

(b) Generic and disease-specific health related quality of life will be measured at baseline, 2 weeks, 3 months, 6 months, 1 year and 2 year follow-up by the EQ-5D, SF-36, Wexner score (for incontinence) and COREFO questionnaires[62].

(c) Costs of TEM and EMR from a societal perspective, based on primary data (see economic evaluation section).

(d) Patient preferences regarding TEM or EMR will be measured at the end of follow-up by a structured questionnaire to enable a discrete choice experiment addressing the burden of care, burden of complications, prognostic uncertainties, and recurrence rates of both treatments.

### Sample size calculation

Assuming a baseline recurrence rate of 3.3% for both TEM and EMR (average recurrence based on a systematic review) and considering an upper limit of 10% for EMR to be non-inferior, with a β-error of 0.2 and α-error of 0.05, 89 patients are needed per randomization group. As unexpected invasive cancers are expected in maximally 3% of patients, the total sample size will be 184 patients.

Since EMR is known to be effective in even more than 2 attempts, an upper limit of 10% seems reasonable, whereas higher recurrence rates would lead to many additional procedures which renders this strategy impracticable and probably not cost-effective.

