#### Cost analysis

The evaluation will include the direct medical costs, out-of-pocket expenses, and the indirect non-medical costs of production loss. The direct medical costs will include the costs of all diagnostic procedures (except study-related ones like anal manometry), therapeutic (repeat) interventions, medication, admissions, day care treatments, specialist consultations, and out-of-hospital care (like general physician, fecal incontinence pads, etc) during follow-up. With approximately over 40% of patients below 65 years of age, production losses will be estimated and based on questionnaire data concerning absence from work and lower efficiency while at work. Out-of-pocket expenses will include the costs of health-related travel, over-the-counter medication, extra washing, etc. Volume data will be gathered with clinical report forms, available hospital information systems, and the Dutch Health and Labour Questionnaire (to be completed by patients at baseline, week 2, and months 3, 12, and 24). The Dutch costing guideline for health care research will be used to determine the relevant unit costs. In case of the TEM and EMR however, micro-costing (general/spinal/conscious anesthesia or sedation, surgical and endoscopic equipment, procedure duration, involved personnel, overhead) in participating centers will be done to estimate real unit costs. The friction costs method will be applied to derive the costs of lost productivity. After price-indexing all costs will be expressed in 2009 euros.

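### At 89 per arm, with about three recurrences expected in each, the stated 80% power and one-sided 5% error do not hold together, and the total of 184 allows only for late cancer exclusions

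*Protocol article*

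**What the plan says.** The Sample size calculation section of the Protocol article gives the planning inputs in one sentence: "Assuming a baseline recurrence rate of 3.3% for both TEM and EMR", "considering an upper limit of 10% for EMR to be non-inferior", and "with a β-error of 0.2 and α-error of 0.05, 89 patients are needed per randomization group". The Abstract (Methods/design) adds that the error rate is one-sided: "beta-error 0.2 and one-sided alpha-error 0.05".

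The total follows from a single adjustment: "As unexpected invasive cancers are expected in maximally 3% of patients, the total sample size will be 184 patients". The Histopathological evaluation section explains it: patients with an unexpected invasive cancer are excluded after pathology, and the expected rate is 1.6–3%.

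The primary outcome is recurrence at surveillance endoscopies at 6, 12 and 24 months. The Data-analysis section compares recurrence proportions by a chi-square test and rules out Kaplan-Meier methods. It names no non-inferiority limit, and no section names the sample size formula.

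**The concern.** A 3.3% rate in 89 patients gives about three recurrences per arm. Normal-approximation formulas for a difference in proportions are unreliable at such counts. The variance is estimated from very few events, and a simple limit can fall below the margin too easily.

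If the printed 80% power is attainable only with a limit whose real error rate exceeds 5%, one of two things follows. Either a positive result carries a larger risk of false non-inferiority than stated, or an inconclusive result is read against power that the design does not have. Separately, the step from 178 to 184 is used up by cancer exclusions, although the outcome needs two years of follow-up.

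**Working it through.** **Inputs.** Recurrence 3.3% in both arms, upper limit 10% for EMR, power 80% and 89 per arm come from the Sample size calculation section. One-sided 5% comes from the Abstract. The limit is read as a margin on the risk difference: 10% − 3.3% = 6.7 points.

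**1. Reproducing 89.** Unpooled normal formula: n = (1.645 + 0.842)² × 2 × 0.033 × 0.967 / 0.067² = 87.9 per arm. With 3.33% and a 6.67-point margin it gives 89.6, so 89 lies within the rounding of the inputs. Other standard choices do not give 89:
- one-sided 2.5%: 112
- 10-point margin: 40
- continuity correction: 116
- Farrington-Manning score formula: 119
- superiority test of 3.3% against 10%: 170 (one-sided) or 216 (two-sided)

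**2. Reproducing 184.** 2 × 89 = 178, and 178 / 0.97 = 183.5, rounded up to 184. The 3% is the whole of the inflation.

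**3. Event counts.** 89 × 0.033 = 2.9 expected recurrences per arm. The chance of none in a given arm is 0.967⁸⁹ = 5.0%.

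**4. Exact operating characteristics at 89 per arm.** Every pair of event counts is enumerated. Non-inferiority is declared when the one-sided 95% upper limit for EMR minus TEM is below 6.7 points (for the score rule, when the equivalent score test rejects). Each pair is weighted by its two binomial probabilities. Power is at 3.3% against 3.3%; the error rate is at EMR 10% against TEM 3.3%.

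| Limit | Power | Error rate |
|---|---|---|
| Wald | 83.2% | 7.4% |
| Score (Farrington-Manning) | 69.2% | 4.5% |
| Newcombe | 73.0% | 5.2% |
| Agresti-Caffo | 76.5% | 5.4% |

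The Wald error depends on the TEM rate: 10.4% if that rate is 1%, and 6.5% if it is 5%. The score error is 4.2% and 4.9% at the same two rates.

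**5. Sensitivity to n.** Exact power is saw-toothed because counts are discrete. The score limit gives 72.7% at 90 per arm and 72.2% at 92. It stays at or above 80% only from about 110 per arm.

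**6. Loss to follow-up (assumed rates; the documents give none).** 184 × 0.97 / 2 = 89.2 per arm after the full 3% of exclusions. Formula power is Φ(0.067 / √(2 × 0.033 × 0.967 / n) − 1.645).

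| Assumed further loss | n per arm | Wald-formula power | Exact score-limit power |
|---|---|---|---|
| 0% | 89.2 | 80.5% | 69% (at 89) |
| 5% | 84.8 | 78.7% | 69% (at 85) |
| 10% | 80.3 | 76.8% | 64% (at 80) |

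**The case against.** The strongest reply is that nothing has been miscalculated. A reader might infer an arithmetic error, but 89 and 184 both reproduce, and normal-approximation planning is common. That stands. The criticism is of the power and error rate that the figures are said to deliver.

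Second, Wald is back-fitted from the answer, and the power depends on a limit that the article does not name and an analysis plan might. This also stands, and it is why a range is given. It does not restore the claim: of the four limits, only Wald reaches 80%, and its error is 7.4%. Newcombe and Agresti-Caffo slightly exceed 5% at this n and still fall short of 80%.

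Third, the 10% could be taken as a fixed ceiling for EMR alone. Four or fewer recurrences in 89 would then give 82.9% power with 4.97% error. But the protocol assumes a rate for both arms, sizes both groups and compares the proportions between them, so the documents do not support a one-arm reading.

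Fourth, the loss argument is easily overstated:
- A reader might infer that any death or missed visit takes the trial below 89 per arm. If cancers occur in 1.6%, 184 × 0.984 = 181 patients remain, three more than 178, and a recurrence already found still counts after a later missed visit.
- The rule "Adenoma recurrence or death will be considered as failure of the treatment strategy" belongs to the outcome of days alive, outside hospital and free of recurrence. It shows that deaths are foreseen, not how many, and does not define the recurrence proportion.
- The remark "With approximately over 40% of patients below 65 years of age" introduces the costing of production losses and says nothing about dropout.

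**Conclusion.** The point holds as a limited one. At 89 per arm, none of the four limits examined combines 80% power with about 5% one-sided error. A Wald limit has 83% power with 7.4% error; limits with error near 5% have about 69–76% power, and the score limit about 69–73% at 89 to 92 per arm. This rests on the protocol's own rates and on reading 10% as a 6.7-point margin, and needs no assumption about dropout. That the protocol used the Wald formula is an inference.

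The missing allowance for death or loss is secondary and conditional. By the protocol's apparent formula, an assumed further loss of 5% or 10% leaves power of about 79% or 77%. With a score limit it is about 69% or 64%. A reader might infer that the real power is about 60%; that would need a score limit combined with an assumed 20% loss, for which the documents give no basis.

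**What to change.** Keep 184 patients and make three changes of wording.

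1. In Sample size calculation, restate the power as roughly 70% (about 69–73%) at 89 evaluable patients per arm, with a one-sided 95% score limit for the risk difference and a 6.7-point margin.
2. Name that score limit as the planning method there, and as the primary non-inferiority analysis in Data-analysis.
3. State that 184 covers late cancer exclusions only and contains no allowance for death or loss to follow-up.

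The cost is a short passage of text and a less favourable stated power. It makes the claim accurate without restoring 80%. For scale, holding 80% with the score limit would take about 110 per arm, or 2 × 110 / 0.97 = 227 patients before any allowance for loss.
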